## Abstract

**Background and aims:**

Parkinson’s disease (PD) is a neurodegenerative disorder for which no disease-modifying therapy currently exists, making it crucial to investigate alternative strategies that may slow its progression. The PRIME study will investigate the effects of combined dietary and physical activity interventions- performed in rehabilitative settings with health professional supervision and evaluation, versus single interventions on the gut microbiome in PD. The aim is to identify microbiome profiles – comparing traditional 16s rRNA gene sequencing with the third-generation method – as potential non-invasive, stage specific biomarkers of PD. In addition, the study will assess whether the combined intervention affects disease progression, symptoms, cognitive abilities, and quality of life.

**Methods:**

Eighty participants with PD will be randomized into four arms: a Mediterranean-diet intervention group; a structured physical-activity group; a combination group receiving both dietary and exercise interventions; a control group receiving standard care only.

**Conclusion:**

By integrating microbiome characterization with the evaluation of these interventions, the study aims to explore whether intervention-induced changes in the microbiota are associated with clinical improvement in PD, thus paving the way for the design of future non-pharmacological protocols to slow disease progression, mitigate symptom severity, and promote diagnosis.

**Clinical trial registration:**

https://clinicaltrials.gov/, identifier NCT07097103.

## Introduction

1

According to the revised definition proposed by Berg et al. (2020), microbiota denotes the complex community of microorganisms inhabiting a given environment (for example, the human gut), including representatives from multiple kingdoms (Bacteria, Archaea, Fungi, Protists, and viruses). By contrast, the microbiome comprises the microbial community together with its “theater of activity” — that is, microbial structural elements, the collective genomes, metabolites and signaling molecules, and the local environmental context that mediate microbe–host interactions. Recent advances in high-throughput sequencing technologies and the development of robust, re-producible bioinformatic workflows have substantially improved taxonomic and functional resolution in microbiome studies and increased the accessibility of large-scale analyses (Knight et al., 2018). Accumulating evidence indicates that the gut microbiome (GM), which is the most extensively studied human microbial community (Cryan et al., 2019), plays a central role in host physiology (Ross et al., 2024; Cryan et al., 2020). Perturbations of the gut microbial ecosystem - known as dysbiosis - have been associated with impaired homeostasis and with a wide range of pathological processes. Mechanistically, the GM may influence the host through multiple complementary pathways that exert immunomodulatory and neuromodulatory effects: production of short-chain fatty acids (SCFAs; e.g., butyrate, propionate), modulation of bile acid pools, generation of tryptophan-derived metabolites, release of microbe-associated molecular patterns such as lipopolysaccharide (LPS), alteration of intestinal barrier integrity, and signaling along the vagus nerve. These mechanisms provide biological plausibility for microbiome–immune–brain interactions, but the relative contribution of each pathway remains to be fully delineated (Cryan et al., 2019).

Bidirectional interaction between the GM and brain-resident immune cells (microglia) have received considerable attention as potential mechanism linking the gut and the brain (Cao et al., 2025). Microglia are the central nervous system’s (CNS) resident innate immune cells; they are highly ramified and plastic and, once activated, can release cytokines and chemokines, express antigen-presenting molecules, modulate neurotransmitter systems and undergo marked morphological and functional changes (Cardinale et al., 2021). Experimental studies in germ-free animals demonstrate that a diverse GM is necessary for normal microglial development and maturation, and that recolonization or administration of microbial metabolites can partially restore microglial phenotype and function (Cryan et al., 2019; Erny et al., 2015). These preclinical findings support the hypothesis that a healthy and diverse GM contributes to the maintenance of microglial homeostasis and, by extension, to normal brain function (Cryan et al., 2019); however, translational extrapolation to humans should be made cautiously. Neurological disorder - a group of conditions affecting the nervous system including CNS and enteric nervous system (ENS) - are characterized by a rage of motor and non-motor symptoms that may reflect interrelated processes of neuroinflammation and neurodegeneration. These mechanisms are tightly interconnected in the development and progression of many neurological disorders, including Parkinson’s disease (PD) (Stolzer et al., 2023). At present, PD is considered a multifactorial disorder with an overall progressive course and no established disease-modifying therapy (Stolzer et al., 2023). Because the GM can influence systemic inflammatory status (Wastyk et al., 2021), interventions that modulate microbiome composition and function may hold therapeutic or preventive potential. Importantly, whereas the human genome is essentially stable throughout life, the microbiome is highly dynamic and responsive to external inputs, rendering it an attractive target for modification (Cryan et al., 2019). Fecal microbiota transplantation from PD patients has been reported to exacerbate disease-related phenotypes in animal models, indicating the presence of specific disease-promoting microbes (Sampson et al., 2016). Moreover, Li et al. (2017) observed PD-associated shifts in the GM — progressive loss of fiber-degraders and gain of putative pathobionts — likely resulting in reduced SCFA levels and increased endotoxin and neuroactive metabolite production. Multiple factors shape the GM across the lifespan, including host genetics, immune interactions, medication use (notably antibiotics), early-life exposures, environmental and geographic influences, sleep and mental health; among these determinants, diet and physical activity are particularly amenable to intervention (Gilbert et al., 2018). A central question motivating this study is whether lifestyle intervention can modify gut micro-biome composition and the systemic inflammatory profile—thereby altering disease progression—and whether microbial signatures that vary with disease stage may serve as early-stage biomarkers.

Despite increasing interest in lifestyle-based strategies to modulate the GM in PD, intervention evidence remains limited and heterogeneous. Studies have evaluated dietary patterns or physical activity separately, but they vary in intervention delivery, intensity, and outcome selection; to our knowledge, this is the first randomized study to evaluate a combined diet-plus-exercise program while concurrently assessing the GM and progression-related clinical outcomes. Moreover, most microbiome studies rely on short-read 16S rRNA sequencing, which may limit taxonomic resolution for biomarker exploration, and longitudinal data beyond end-of-intervention are scarce. PRIME was designed to address these gaps through a multicenter randomized factorial pilot trial comparing Mediterranean diet, intensive physical activity, and their combination versus standard care, with a prespecified primary microbiome endpoint and exploratory follow-up assessments.

## Study objectives

2

The Parkinson’s Research In Metagenomic Early-stage biomarkers (PRIME) study aims to evaluate the impact of a combined dietary and physical activity intervention, performed in rehabilitative settings with health professional supervision and evaluation, compared with each single intervention (diet and physical activity alone), on the GM of patients with PD, with the ultimate goal of identifying a specific microbiome profile that could serve as an non-invasive, stage-specific biomarkers. The study will also explore whether the combined intervention modifies are associated with the disease progression, as measured by changes in motor and non-motor symptoms (including gastrointestinal manifestations), cognitive performance, and health-related quality of life.

## Materials and methods

3

### Study design and setting

3.1

The PRIME study is a 6-month, parallel-group, four arm, open-label pilot trial employing a 2 × 2 factorial, randomized, multicenter, controlled design conducted in accordance with the SPIRIT guidelines (Chan et al., 2025; Figure 1 and Supplementary Table 1).

**FIGURE 1 F1:**
[figure not shown]
Schedule of enrollment, interventions, and assessments (SPIRIT figure). X indicates that the corresponding assessment and/or biological sample collection will be performed at that time point.

This multicenter study will be conducted at two Parkinson’s Disease Centers located at IRCCS San Raffaele Roma (RU1), which will serve as the Coordinating Center, and San Raffaele Cassino (RU2), as a participating clinical site. The study will be carried out in close collaboration with academic centers of San Raffaele University of Rome (RU3); Northwestern University (Evanston, Chicago, IL, United States) (RU4); University of Urbino Carlo Bo (RU5), that will act as partner research sites.

The study protocol was reviewed and approved by the Ethics Committee of Lazio Area 5 (RP 340/SR/25; Protocol version 1.0; number: 0009232, date 19 June 2025). The trial will be conducted in accordance with the Declaration of Helsinki and with applicable data protection laws, including the General Data Protection Regulation (EU) 2016/679 (GDPR). Before enrolling in the trial, each participant will be comprehensively informed about the study’s objectives, procedures, potential risks, and benefits. Adequate time will be provided for individuals to ask questions, receive clarifications, and consider their decision. Participation will be entirely voluntary, and only upon the signature of a study-specific consent form, will the individual be included in the trial.

This protocol was drafted solely on the basis of clinical and scientific expertise without direct patients or public involvement, although we recognize the importance of such engagement in research.

The trial will follow CONSORT guidelines (Schulz et al., 2010) and has been registered on ClinicalTrials.gov (NCT07097103; registered 30 July 2025) in accordance with the International Committee of Medical Journal Editors (ICMJE) recommendations. Supplementary Figure 1 shows the planned participant flow diagram (Hopewell et al., 2025) in line with CONSORT recommendations that illustrated the expected enrollment, allocation, follow-up and analysis stages for the trial. The full completed diagram will be presented with the final trial results.

### Participants and eligibility criteria

3.2

The calculation of the sample size was not strictly required given the pilot nature of this study. Accordingly, the target sample size was primarily driven by feasibility considerations and the need to obtain precise effect-size estimates to inform a definitive RCT. However, to support the microbiome endpoint, we performed an *a priori* power assessment. Following the recommendations of Ferdous et al. (2022), we selected β-diversity as the primary endpoint to detect differences between groups in the composition of intestinal microbial species. Using G*Power version 3.1.9.7, assuming an effect size of (Cohen’s f) 0.25, a statistical power of 0.95 (1−β) and setting α to 0.05, we estimated the minimum required sample size. To account for expected attrition during the intervention and follow-up period (approximately 10%), the total sample size was increased to 80 participants (20 per arms). Participants will be recruited from Clinical Trial Centers for Parkinson’s Disease (RU1 - RU2) during routine clinical visits. A total of eighty (*n* = 80) participants meeting the following eligible criteria will be enrolled and randomly assigned to an intervention or to the control group:

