#### Primary outcome

3.5.1

The primary endpoint of the PRIME study is to evaluate the effect of the interventions on GM β-diversity in PD patients, defined as the change in Bray-Curtis dissimilarity from T0 (baseline) to T1 (end of intervention). The prespecified primary contrast will be the between-group difference in the T0-T1 change in β-diversity for the combined intervention (Group C) versus standard care (Group D). As supportive primary microbiome descriptors, we will also quantify α-diversity and taxonomic composition/relative abundance, with analyses primarily intended to describe community structure and to support interpretation of β-diversity findings. Microbiome profiling will be performed using third-generation, high-resolution long-read sequencing technology, the Pacific Biosciences (PacBio) system, capable of sequencing amplicons up to ∼20,000 base pairs (bp) (Biada et al., 2025; Buetas et al., 2024). Exploratory microbiome aims will include (i) identification of stage-associated microbial patterns and candidate non-invasive microbiome biomarkers, treated as hypothesis-generating, and (ii) a methodological comparison between PacBio long-read sequencing and Illumina MiSeq short-read 16S rRNA amplicon sequencing. The comparison will evaluate relative performance in terms of taxonomic resolution and community profiling, with particular attention to the ability of PacBio to achieve higher resolution at the species level. We will also assess the degree of compositional similarity between microbial communities characterized by the two platforms, thereby determining the feasibility and potential benefits of integrating sequences from different technologies in microbiome research. FU1 and FU2 assessments will be used for exploratory analyses of the durability/maintenance of microbiome changes beyond the end of the intervention. Results from these exploratory analyses will be interpreted in the context of the pilot design.

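### The power of 0.95 at f = 0.25 is attached to the four-arm total of 80 and is not shown for the primary contrast of Group C with Group D, which uses half of that sample

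*Protocol article*

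**What the plan says.** Section 3.2 of the Protocol article calls the trial a pilot, says that a sample-size calculation was not strictly needed, and rests the target mainly on feasibility and on "the need to obtain precise effect-size estimates to inform a definitive RCT". It then offers a power assessment in support of the microbiome endpoint. The endpoint is introduced with the words "we selected β-diversity as the primary endpoint to detect differences between groups in the composition of intestinal microbial species", with no pair of arms named. The effect size and power are given as "assuming an effect size of (Cohen’s f) 0.25, a statistical power of 0.95". The significance level follows in the same sentence: "setting α to 0.05, we estimated the minimum required sample size". After an allowance of about 10% for attrition, "the total sample size was increased to 80 participants (20 per arms").

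Section 3.5.1 fixes the contrast: "The prespecified primary contrast will be the between-group difference in the T0-T1 change in β-diversity for the combined intervention (Group C) versus standard care". The comparator arm is Group D. Section 4.1 names the test as PERMANOVA on Bray-Curtis dissimilarity, comparing C with D from T0 to T1. Section 4 sets p < 0.05 as the criterion for the primary analysis.

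**The concern.** The power statement refers to the whole trial and the primary test uses two of its four arms. A reader who meets 0.95 in a paragraph written to support the primary endpoint will naturally take it as the power of the primary test. A non-significant C versus D result could then be read as stronger evidence against an effect than the data can give. The same paragraph promises precise effect estimates for planning a definitive trial. If those come from about 18 participants per arm, the later trial could be sized on a much less certain figure than the word suggests.

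**Working it through.** **Inputs from the Protocol article.** f = 0.25, power 0.95, α = 0.05, attrition about 10%, 80 randomised, 20 per arm (section 3.2); allocation 1:1:1:1 (section 3.4.1); primary contrast C versus D on T0-T1 change (sections 3.5.1 and 4.1).

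**Counts.** All arms: 80 × 0.9 = 72 completers. C and D: 40 × 0.9 = 36, or 18 per arm.

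**Assumed.** The type of F test, the number of visits m and the correlation ρ between visits, none of which is given. All power figures below use the noncentral F distribution.

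**Step 1: which test could give about 72?**
- One-way ANOVA, λ = f²N. Four groups need N = 280, and power at 72 is 0.38. Two groups need 210. Neither fits.
- Repeated-measures group-by-time interaction with k groups, λ = f²Nm/(1 − ρ), degrees of freedom (k − 1)(m − 1) and (N − k)(m − 1). For k = 4, m = 2, ρ = 0.5, N = 72: λ = 0.0625 × 72 × 2/0.5 = 18.0 on 3 and 68 df, power 0.948. The minimum N for 0.95 is 73, or 76 in equal arms, so the match is close but not exact. 72/0.9 = 80.
- The same test with k = 2, m = 2, ρ = 0.33 also gives N = 72 (power 0.951).
- With k = 2, m = 4, ρ = 0.5 it gives N = 36 (power 0.952), and 36/0.9 = 40.

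So more than one setting is compatible with the sample size, and the source of the 0.95 cannot be deduced.

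**Step 2: the primary contrast with the four-arm inputs.** k = 2, m = 2, N = 36, ρ = 0.5: λ = 0.0625 × 36 × 2/0.5 = 9.0 on 1 and 34 df, power 0.83. Over assumed ρ:

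| ρ | λ at N = 36 | Power, N = 36 | Power, N = 40 |
|---|---|---|---|
| 0 | 4.50 | 0.54 | 0.59 |
| 0.3 | 6.43 | 0.69 | 0.74 |
| 0.5 | 9.00 | 0.83 | 0.87 |
| 0.7 | 15.00 | 0.96 | 0.98 |

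Power of 0.95 at N = 36 needs ρ of about 0.67. At ρ = 0.5 it needs 54 completers in C and D together.

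**Step 3: other origins of the figure.**
- If 72 came from the two-group, two-visit test at ρ of about 0.33, power at 36 is 0.71.
- The two-group, four-visit test does give 0.95 at 36. It uses FU1 and FU2 as well, so it is not the T0-T1 contrast, and it fits poorly with a total that was raised to 80.
- If f = 0.25 is the spread of four arm means, the implied C-D effect depends on the pattern. With equal additive effects the means are 0, a, a, 2a with SD a/√2, so a = 0.354 SD and the two-group f for C versus D is also 0.354: power 0.985 at ρ = 0.5. With an effect in C only, the mean b has SD b√3/4, so b = 0.577 SD and f = 0.289: power 0.92.

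**Step 4: precision.** For a continuous outcome compared at 18 per arm, the 95% half-width is t(0.975, 34) × √(2/18) = 2.032 × 0.333 = 0.68 SD. With 20 per arm it is 2.024 × √(2/20) = 0.64 SD.

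**Limit.** These are univariate F-test approximations. A Bray-Curtis PERMANOVA has no direct Cohen's f, so its power could differ in either direction.

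**The case against.** The strongest reply is that this is a pilot whose size rests on feasibility, that the calculation is offered only as support, and that software settings are normally left to the full protocol. All of that stands. The missing settings are not the point here, and no printed figure can be called miscalculated. What remains is that the article itself prints a power beside a four-arm total and fixes a two-arm primary contrast elsewhere.

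The reply can add that C versus D may in fact have 0.95. That is true at ρ of about 0.67 or more, or with an additive four-arm reading of f at ρ = 0.5. The article states none of these conditions. It is also fair that 18 per arm is cautious: the 10% covers follow-up to week 48, while the primary endpoint is at week 24 and the analysis is mainly by intention to treat. With all 40, power at ρ = 0.5 is 0.87.

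Three stronger readings are tempting and are not supported:
- A reader might infer that the 0.95 must come from an omnibus test over all four arms. Step 1 shows two-group settings that also give 72 or 36.
- A reader might take 0.31, the power of a two-group comparison of single-visit values at 36 with f = 0.25, as the power of the primary test. The primary endpoint is a T0-T1 change, so that figure describes a different analysis.
- A reader might conclude that the primary contrast certainly lacks 0.95. Without ρ or the effect pattern, the article permits only the statement that this power is not shown.

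**Conclusion.** The concern holds as a mismatch between section 3.2 and sections 3.5.1 and 4.1: 0.95 is stated for a total of 80 and is not shown for the contrast that the trial will test. With the four-arm, two-visit reconstruction at ρ = 0.5, C versus D has about 0.83 (36 completers) to 0.87 (40). The range at 36 is 0.54 to 0.96 for ρ from 0 to 0.7. The size of the gap rests on assumed inputs and on a univariate approximation. The counts of 72 and 36 follow directly from the article's own figures. The word precise is hard to sustain with a half-width of about 0.68 SD. Given the pilot and feasibility framing, and since neither the sample size nor the analysis changes, this should be corrected but is not critical.

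**What to change.** 1. Keep 80 participants, justified by feasibility.
2. Either stop presenting 0.95 as the power that supports the primary endpoint, or state the comparison it belongs to, with the test, number of groups, number of visits and correlation used.
3. Report power for C versus D at about 18 to 20 per arm. Preferably simulate the Bray-Curtis PERMANOVA and state the assumed R² and T0-T1 correlation. Label any univariate figure, such as 0.83 at ρ = 0.5, as an approximation.
4. Replace the claim of precise estimates with the expected precision: for a continuous outcome, a 95% half-width of about 0.68 SD at 18 per arm.

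The cost is wording and a small simulation, with no extra participants. The stated power will probably look less favourable.

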#### Inclusion criteria

3.2.1

Males and females aged 35–80 with a diagnosis of Parkinson’s disease according to the United Kingdom (UK) Parkinson’s Disease Society Brain Bank criteria (Gibb and Lees, 1988);Disease stage I-III in the “ON” phase, as defined by the modified Hoehn and Yahr (H&Y) scale (Hoehn and Yahr, 1967);No severe cognitive impairment according to the Mini-Mental State Examination score (MMSE ≥ 24) (Folstein et al., 1975) and the Montreal Cognitive Assessment score (MoCA ≥ 17.54/30) (Santangelo et al., 2015);Stable dopaminergic pharmacological treatment (for at least 4 weeks prior to screening);Suitable for physical exercise and able to walk unassisted (no walking aids);Willingness to maintain usual diet during a ≥4-week run-in period;Willingness to adopt a Mediterranean style diet during the intervention;Ability to provide stool samples at each collection timepoint;Willingness to abstain from strenuous exercise and alcohol for 24 h before each study visit;Ability to interact with the research team and provide informed consent in Italian language;Willingness and ability to comply with all study procedures.

#### Exclusion criteria

3.2.2

Atypical or secondary Parkinsonism;Pre-existing psychiatric disorders or dementia diagnosis;Implanted subcutaneous electronic device (e.g., pacemaker);History of deep brain stimulation (DBS) surgery;Moderate to severe cognitive impairment;Beck Depression Inventory II (BDI II) score ≥ 28;Active serious illness (e.g., thyroid dysfunction, type 2 diabetes with HbA_1_c ≥ 8% or on insulin, active malignancy, type 1 diabetes) or unstable condition requiring medical dietary supervision (e.g., IBD, IBS, celiac disease);Acute medical illness (including antibiotic-resistant infections);Major gastrointestinal surgery or acute gastrointestinal conditions (e.g., gastroenteritis) within the past 3 months;Chronic corticosteroid therapy;Use of proton pump inhibitors within the past 30 days;Antibiotic intake within the past 30 days;Prebiotic and/or probiotic use within the past 30 days;Prolonged use (≥3 months) of anxiolytic drugs, antidepressants, antipsychotics, cognitive stimulants, or analogues;Underweight: body mass index (BMI) < 18.5 kg/m^2^;Pregnancy or lactation;Regular use of enemas or suppositories for constipation;Participation in other experimental protocols within 3 months of screening;Requirement for special dietary regimens incompatible with Mediterranean diet (e.g., strict vegan or vegetarian patterns).

